## 9.4 Breastfeeding

Currently, it is unknown if there are any effects of Acidform lubricant on breast-milk. Though it is unlikely that the gel will pass through breast milk, systemic absorption of the gel into the blood may affect breast milk and cause harm to an infant. Therefore, participants who are breastfeeding will be excluded from participation in the study.

**9.5 Criteria for Discontinuation**

Accrual into this study will be suspended if two or more participants in the same arm experience similar grade 3 or higher AEs (as defined by the Female Genital Grading Table for Use in Microbicide Studies and the DAIDS Table for Grading the Severity of Adult and Pediatric Adverse Events, Version 1.0, December 2004) judged possibly, probably, or definitely related to product use. The protocol team in collaboration with the Safety Committee and NIH NIAID/DAIDS Medical Officer then will review all pertinent data and determine whether to continue accrual and product use. The team may decide to stop the study at this time, or at any such time that the team agrees that an unacceptable type and/or frequency of AEs have been observed.

The study may be discontinued at any time by the IRB, the NIH, the pharmaceutical supporters or designees, the Office for Human Research Protections (OHRP), or other government agencies as part of their duties to ensure that research subjects are protected.

Monitoring of AEs will be ongoing through regular reviews (safety monitoring). If needed, the protocol team will convene ad hoc meetings in the event of an abnormal number of reported AEs judged definitely, probably, possibly, or probably not related to study gel or applicator, or any other conditions deemed as an emergency event by team members.

**9.6 Criteria for Permanent Treatment Discontinuation for an Individual Participant**

The criteria for permanent treatment discontinuation of further study product/intervention(s) for an individual participant are:

- Treatment-related toxicity (see section 9), including pelvic inflammatory disease, deep epithelial disruption
- Requirement for prohibited concomitant medications such as oral or intravenous antibiotics
- Pregnancy or breastfeeding
- Completion of treatment as defined in the protocol
- Request by participant to terminate treatment
- Clinical reasons believed life-threatening by the physician even if not addressed in the toxicity section of the protocol
- Unwillingness or inability to remain abstinent for the duration of the study.

The participant will continue to be followed with participant’s permission if study product/intervention(s) is discontinued.

**9.7 Criteria for Premature Study Discontinuation for an Individual Participant**

The criteria for premature discontinuation from the study for an individual participant are:

- Pregnancy or breastfeeding
- Request by participant to withdraw
- Request of the primary care provider if s/he thinks the study is no longer in the best interest of the participant
- Participant judged by the investigator to be at significant risk of failing to comply with the provisions of the protocol as to cause harm to self or seriously interfere with the validity of study results
- At the discretion of the IRB, OHRP, NIH, investigator, or pharmaceutical supporter.

## 10.0 STATISTICAL CONSIDERATIONS

## 10.1 Overview and Statistical Designs Issues

## All subjects who receive treatment (Acidform lubricant or HEC placebo gel) will be included in all analyses. The primary objective of this study is to compare the safety of Acidform lubricant to HEC gel by assessing the genital tract mucosal response to 14 days of twice daily application by measuring endogenous antimicrobial activity and levels of mediators of host defense, including defensins, cytokines and chemokines in CVL. The clinical safety of Acidform when administered twice daily for 14 consecutive days will be assessed by also including the following endpoint: Grade 2 or higher adverse experiences judged by the Investigator to be possibly, probably, or definitely related to product use.

Differences between groups with respect to age and baseline amounts of immune mediators will be compared by *t* test. Differences between groups with respect to endogenous antimicrobial activity of CVL against HSV and *E. coli* and change in mucosal immune mediators will be compared by analysis of covariance and adjusted for baseline (after log transformation of data for cytokines, chemokines, and mucosal mediators). Differences between groups with respect to change in percentage reduction in viral or bacterial infection after application of drug or placebo gel relative to titers in screening CVL samples will be determined by Wilcoxon nonparametric test (with exact p-values).

All visits in which a woman has been exposed to the study product will be included in the analysis of clinical safety. The number and the percentages of participants experiencing at least one Grade 2 or higher AE, and the number and percentage experiencing each specific AE will be tabulated by study arm. Each participant will contribute once in each category (i.e. only for highest severity AE for each participant) for the calculation of event rates. The number and percentage of participants experiencing a Grade 2 or higher AE will be tabulated by severity and relationship to treatment for each treatment group. AEs that lead to study product discontinuation will be listed in a separate data listing. The number and percentage of participants with a Grade 2 or higher AE judged possibly, probably or definitely related to study treatment will be summarized and compared for each treatment group by Fisher’s exact test.

An additional objective is to assess whether a single dose of Acidform lubricant or HEC present in CVL 2 hours after intravaginal application reduces HIV and HSV *in vitro*. Differences between the groups with respect to log reduction in HIV or HSV infection after application of Acidform or HEC relative to titers in baseline CVL samples will be determined by Wilcoxon nonparametric test (with exact p values).

[name] will provide statistical support through the Biostatistical Core at the GCRC and the Institute for Clinical and Translational Research at AECOM/MMC. Statistical analyses will be performed with STATA software (Version 10, STATA Corp.).

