The goal of this proposed non-network clinical trial, which is sponsored by the Integrated Preclinical/Clinical Program for HIV Topical Microbicides PAR 03-137 is to compare the genital tract mucosal response to 14 days of twice daily application of Acidform lubricant to HEC gel by measuring endogenous antimicrobial activity and levels of cytokines, chemokines, defensins and other protective proteins in cervicovaginal lavage (CVL). Exploratory objectives include determining whether intravaginal application of Acidform lubricant or HEC results in alterations in epithelial integrity, examining changes in vaginal flora and examining the the antiviral activity of Acidform lubricant by evaluating the ability of CVL collected 2 hours after a single application of Acidform or HEC to inhibit both HIV and HSV using a spiking strategy developed in our laboratory. These studies should help determine whether Acidform would serve as an appropriate vehicle for formulation of candidate acid-stable microbicides.

This study builds on our previous work in which we tested the effect of 14 days of daily application of 0.5% PRO 2000 gel, a naphthalene sulfonic acid polymer currently in Phase IIB/III clinical trials, on levels of inflammatory, anti-inflammatory and protective immune mediators and on the endogenous antimicrobial activity of cervicovaginal fluid (11). Cytokines and chemokines were lower and protective factors including IL-1 receptor antagonist (IL-1ra), immunoglobulins, secretory leukocyte protease inhibitor (SLPI) and human beta-defensin (HBD) 2 were reduced in CVL in the PRO 2000 compared to the placebo group on Days 7 and 14, but returned towards normal on Day 21 (7 days after the last exposure to drug). Importantly, the modest reduction in protective factors was not associated with any detectable loss in the endogenous antiviral (HIV or HSV) or antibacterial (*E. coli* or *Staphylococcal aureus*) activity in CVL samples. We hypothesize that inclusion of measurement of endogenous antimicrobial activity or levels of specific mediators in CVL in Phase I clinical studies may provide biomarkers predictive of safety.

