## 3.0 OBJECTIVES

## 3.1 Primary Objective

The primary objective of the study is to compare the safety of Acidform lubricant to HEC gel by assessing the genital tract mucosal response to 14 days of twice daily application by measuring endogenous antimicrobial activity and levels of mediators of host defense, including defensins, cytokines, and chemokines in CVL.

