Every effort will be made to bring participants back after 7 and 14 doses of Acidform or HEC. Visits will be scheduled in the GCRC on Day 7 (range, days 5-9) and Day 14 (range, days 12-15). For study visits conducted on Day 7 and 14, subjects will be instructed to apply the morning dose after the study visit is completed. There will be a Final Visit scheduled on Day 21 (range, days 16-21), prior to the anticipated onset of menstruation. A pelvic exam will be performed and vaginal pH will be measured at each visit. CVL samples will be obtained at the Screening Visit, Enrollment Visit (2 hours after the application of Acidform or HEC), and on Days 7, 14, and 21. A cytobrush for measurement of immune cell populations and a vaginal swab for assessment of vaginal flora will be collected at Enrollment (prior to application of Acidform or HEC), Day 14 and Day 21. [name] or [name] will collect one cervical biopsy colposcopically at the Day 14 visit for assessment of epithelial integrity. Participants will be instructed to document symptoms of vulvar or vaginal soreness or pruritus, vaginal bleeding, dysuria, or acts of vaginal penetration in a study diary, which will be provided. Participants will be asked to record information on the number of times they administer study gel, time of each insertion, emergence/resolution of specific symptoms and reasons for non-adherence. Diaries will be reviewed at each visit. Participants will bring used and unused supplies with them to each visit for counting and disposal. Adverse events will be recorded as described in Section 8.0. Subjects will receive $25 at the Screening visit. An additional $25 will be given at Screening if a biopsy is performed. Fifty dollars will be provided at the Enrollment, Day 7, Day 14 and Day 21 study visits. An additional $50 will be given for completion of a biopsy at the Day 14 study visit. A total of $300 will be provided for completion of all study visits as compensation for their time and travel expenses.

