**4.1 Laboratory Methods**

The vaginal pH will be measured using an electronic ISFET pH meter. A stainless steel sensor pH probe will allow us to measure the pH in different locations in the vagina. There is less variability with the probe compared to pH paper, which has been used in most of the previous studies. We will measure pH at Screening, Enrollment (prior to and 2 hours after the first application of Acidform or HEC), Day 7, Day 14 and Day 21.

CVL will be immediately transported on ice to the investigators’ laboratories and centrifuged for 20 minutes at 1000 g at 4C, aliquoted and stored at -80C. CVL will be collected using 10 ml of normal saline. We have demonstrated that Acidform gel retains its low pH (~ 3.5) when mixed 1:10 with normal saline. Thus, collection of CVL in normal saline should not interfere with the buffering effects of Acidform. Cytobrush specimens will be transported on ice to the lab. The cells will be gently dislodged, centrifuged and immediately frozen in fetal bovine serum with 10% dimethyl sulfoxide. The cells will be thawed at a later date, counted, washed, respun and stained using a panel of differentially conjugated mAbs against various human leukocyte membrane antigens and analyzed by fluorescent activated cell sorter (FACS). Cell preparations will be labeled in parallel with appropriate isotype control Abs (Becton-Dickinson).

Cytokines and chemokines in CVL supernatants will be quantified using a multiplex Luminex assay (Millipore), which allows for the quantitative measurement of multiple cytokines or chemokines using a small sample size. The following mediators will be measured by Luminex: IL-1, IL-1, IL-2, IL-6, IL-8, IFN-, IFN-, and RANTES. IgG, IgA, SLPI, IL-1ra, lactoferrin, lysozyme and HNP1-3 also will be measured using commercial ELISA kits (R & D Systems, Minneapolis, MN). These mediators were selected because of their potential to influence mucosal immunity. The total protein concentration will be measured and the results will be presented per mg of protein in CVL as well as per ml of CVL to control for any differences in CVL collection. To determine whether Acidform or HEC interferes with the detection of any of the mediators, standards will be diluted in saline or saline containing Acidform or HEC gel (2 ml of Acidform or HEC added to 10 ml of normal saline) and results will be compared.

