**10.2 Sample Size Considerations**

There is limited data regarding intra- and inter-subject variability of endogenous antimicrobial activity detectable in CVL. We recently completed a pilot study that included measuring endogenous antimicrobial activity and immune mediators in CVL collected weekly for 2 months from healthy women who were either naturally cycling or receiving hormonal contraception. Among 9 cycling women, the mean percentage inhibition of HSV infection (defined as the viral plaque formation in cells treated with CVL as a percentage of plaque formation in the presence of control fluid) at the initial visit was 54 with a standard deviation (sd) of 28. The sd is the same if we use the mean of all samples collected from the cyclers (n=52). If we assume that Acidform and HEC have no impact on endogenous anti-HSV activity and consider 28 (1 sd) as functionally equivalent, a sample size of 18 subjects per arm will provide 80% power to observe statistically significant equivalence of means. This sample size is similar to other Phase I studies of topical microbicide products.

The following table represents the probability of observing zero, at least one, and two or more adverse experiences among the sample size of 18 using Acidform for various “true” event rates:

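### The primary objective spans 17 CVL measures at three post-dose visits with no deciding measure or visit, and the one sized contrast (equivalence of anti-HSV activity) is neither declared primary nor matched by an analysis

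*Protocol*

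**What the plan says.** Section 3.1 states the primary objective as a comparison of safety through the mucosal response to 14 days of use, by "measuring endogenous antimicrobial activity and levels of mediators of host defense, including defensins, cytokines, and chemokines in CVL". Section 10.1 repeats this almost word for word: "measuring endogenous antimicrobial activity and levels of mediators of host defense, including defensins, cytokines and chemokines in CVL".

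Section 4.1 gives the content of that set. Eight mediators come from the multiplex assay ("The following mediators will be measured by Luminex", followed by the list) and seven from ELISA: "IgG, IgA, SLPI, IL-1ra, lactoferrin, lysozyme and HNP1-3 also will be measured using commercial ELISA kits". Endogenous activity is assayed against HSV and E. coli. For mediators, "the results will be presented per mg of protein in CVL as well as per ml of CVL".

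Section 4.0 schedules CVL at screening and at the "Enrollment Visit (2 hours after the application of Acidform or HEC), and on Days 7, 14, and 21". Section 7.1 assigns the two-hour Day 0 sample to the spiking studies, which are exploratory under 3.3. That leaves three post-dose visits for the primary set.

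Section 10.1 compares the arms by baseline-adjusted ANCOVA for antimicrobial activity and for the mediators. It then adds a Wilcoxon test on the change in percentage reduction of viral or bacterial infection relative to screening. It also adds related Grade 2 or higher adverse events as a clinical safety endpoint, compared by Fisher's exact test.

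Section 10.2 takes anti-HSV inhibition (mean 54, sd 28 in nine cycling women), treats 28 points as functionally equivalent, assumes no true effect, and concludes that "a sample size of 18 subjects per arm will provide 80% power to observe statistically significant equivalence of means".

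**The concern.** Three parts of the plan do not meet. The objective is a whole set of measures. The analysis is a series of difference tests on that set. The sample size is for equivalence on one member of it. Nothing says which result answers the primary question, at which visit, or whether the answer is an absence of significant differences or a demonstration of equivalence.

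The protocol's own background shows that members of the set can move separately. In the earlier PRO 2000 study (Section 2.1), cytokines, chemokines and protective factors were lower on Days 7 and 14 and returned towards normal on Day 21, yet "the modest reduction in protective factors was not associated with any detectable loss in the endogenous antiviral" or antibacterial activity. If Acidform behaved in the same way, the primary result could be reported from the mediators or from the activity assays, and that choice would be made after the data are seen.

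The 80% power is also exposed. It belongs to a contrast that the objective does not single out and that the analysis section does not carry out.

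**Working it through.** **1. Size of the set.** 8 multiplex + 7 ELISA + 2 activity assays = 17 measures. 17 × 3 visits = 51 measure-by-visit contrasts, if each visit is analysed separately.

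**2. The plan's own power.** Inputs from 10.2: n = 18 per arm, sd 28, margin 28, true difference 0. Alpha is not stated.
- Standard error = 28 × √(2/18) = 9.33, so margin/SE = 3.00.
- Two one-sided tests at 5%, normal approximation: 2Φ(3.00 − 1.645) − 1 = 0.825.
- With the t distribution (34 df), averaging over the sampling distribution of the sd: 0.804.
- At one-sided 2.5%, the t-based figure is 0.66.

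The stated 80% is therefore reproduced, for one contrast, at one-sided 5%.

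**3. Chance of at least one false difference.** Assume two-sided 5% per test, no true effect, and the same correlation ρ between all test statistics. Neither alpha nor ρ is in the protocol.
- Independent tests: 1 − 0.95^17 = 0.58 and 1 − 0.95^51 = 0.93.
- Correlated tests: 1 − ∫ φ(u) [Φ((1.96 − √ρ·u)/√(1−ρ)) − Φ((−1.96 − √ρ·u)/√(1−ρ))]^k du.

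| ρ | 17 measures, one visit | 51 measure-by-visit tests |
| --- | --- | --- |
| 0 | 0.58 | 0.93 |
| 0.5 | 0.39 | 0.63 |
| 0.8 | 0.21 | 0.30 |
| 0.9 | 0.15 | 0.19 |

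A simulation with separate correlations between measures (0.5) and between visits (0.5) gave higher values, 0.42 and 0.74. There, different measures at different visits are less alike than equal correlation assumes.

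**4. Power if equivalence were required on every measure.** Simulated two one-sided tests, 18 per arm, margin 1 sd, true difference 0, one-sided 5%, equal correlation 0.5:
- 1 measure: 0.80
- 2 measures: about 0.67
- 6 measures: 0.38
- 17 measures: about 0.12 to 0.13 across runs

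For all 17, the figure is 0.03 at correlation 0 and 0.40 at correlation 0.8.

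**5. Analysis against sizing.** Section 10.2 needs a test or interval set against ±28. Section 10.1 contains none. It gives antimicrobial activity two difference tests instead, ANCOVA and Wilcoxon, without saying which one governs.

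**The case against.** Several points against the concern stand.
- This is a Phase I study whose rationale is that surrogate markers of safety are not yet established. The protocol nowhere says that any p < 0.05 counts against Acidform, or that every measure must be equivalent. The error and joint-power figures show what would follow from such rules. They do not describe rules the plan adopts.
- A reader might infer that a chance difference is likely. That depends on an unstated alpha and unknown correlations; at correlation 0.9 the figures are 0.15 and 0.19.
- A reader might count 96 tests by doubling the mediators: (15 × 2 + 2) × 3. Section 4.1 says only that both scales will be presented, and 10.1 does not say both will be tested. The choice of scale, and any false-discovery handling, can properly be left to an SAP.
- The PRO 2000 pattern does not show that opposite verdicts would be equally supported. The protocol reports it as one coherent finding, and Day 21 there was seven days after the last exposure, so it shows recovery.
- Anti-HSV activity is the only CVL measure sized, and the objective speaks of 14 days, so Day 14 anti-HSV activity is the natural candidate.

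The last point supports the fix but does not close the gap. Sections 3.1 and 10.1 give anti-HSV activity no precedence, and the 14 days describe exposure, not an analysis visit. An SAP may hold the detail, but the primary measure and visit define the objective and the power claim. Both are stated in this protocol, and they do not agree.

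**Conclusion.** The concern holds in a limited form. The protocol makes 17 measures at three post-dose visits primary, tests differences, and sizes one equivalence contrast that is undeclared, has no visit and has no matching analysis. That conclusion rests on the text alone and needs no assumption about alpha or correlation.

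The size of the consequence does need assumptions. At 5% two-sided with no true effect, a false difference somewhere has probability 0.15 to 0.58 (17 tests) or 0.19 to 0.93 (51 tests), that is, about 3 to 19 times a 5% level (0.15/0.05 to 0.93/0.05). The 80% power is sound for a single contrast at one-sided 5% and does not extend to the set. The documents do not support the stronger claim that a false safety signal is to be expected. The change should be made, but nothing here invalidates the design.

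**What to change.** - **3.1 and 10.1:** name one primary contrast, the arm difference in baseline-adjusted anti-HSV activity at Day 14. Analyse it by ANCOVA and compare the 90% confidence interval for the difference with the ±28 margin already in 10.2. Make the Wilcoxon test on the same measure a sensitivity analysis.
- **10.2:** state that the 80% power applies to this contrast only, at one-sided 5%.
- **Secondary safety measures:** E. coli activity, the 15 mediators, Days 7 and 21, and the comparison of related Grade 2 or higher adverse events. Report all of them in full, with estimates and confidence intervals and without multiplicity adjustment, so that no signal is hidden.
- **Interpretation:** read the primary result beside these measures. Section 4.1 concedes that residual gel may contribute to the activity measured in CVL, and Section 2 describes Acidform as active against HSV, so preserved activity at Day 14 alone could mask a loss of endogenous defence.

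The cost is wording in three sections, with no added participants, samples or assays. It does require the sponsor to commit to one measure within the present objective. The downside is that an isolated mediator difference could no longer be presented as the primary result.

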**10.2 Sample Size Considerations**

There is limited data regarding intra- and inter-subject variability of endogenous antimicrobial activity detectable in CVL. We recently completed a pilot study that included measuring endogenous antimicrobial activity and immune mediators in CVL collected weekly for 2 months from healthy women who were either naturally cycling or receiving hormonal contraception. Among 9 cycling women, the mean percentage inhibition of HSV infection (defined as the viral plaque formation in cells treated with CVL as a percentage of plaque formation in the presence of control fluid) at the initial visit was 54 with a standard deviation (sd) of 28. The sd is the same if we use the mean of all samples collected from the cyclers (n=52). If we assume that Acidform and HEC have no impact on endogenous anti-HSV activity and consider 28 (1 sd) as functionally equivalent, a sample size of 18 subjects per arm will provide 80% power to observe statistically significant equivalence of means. This sample size is similar to other Phase I studies of topical microbicide products.

The following table represents the probability of observing zero, at least one, and two or more adverse experiences among the sample size of 18 using Acidform for various “true” event rates:

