**10.3 Enrollment/Randomization/Blinding Procedures**

The randomization will be 1:1 (i.e., 18 in each treatment arm). The AECOM Research Pharmacy will provide the randomization procedure for both clinical sites. Subjects will be given the choice of selecting a clinical site. A specific number of women is not required at each site. Throughout the period of study implementation and data analysis, the [name] laboratory team will not be informed of the participants’ random assignments. Although the clinical study team will be aware of the participants’ assignment to either Acidform or HEC, the lab staff will perform all proposed testing blindly.

Both study gels will be supplied in single-use tubes, and single-use applicators packaged in individual wrappers. Lab staff will be unblinded after all study visits and data analyses are completed.

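### The trial is sized to show equivalence of anti-HSV activity within ±28 points, but Section 10.1 plans only tests of difference and never uses the margin

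*Protocol*

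**What the plan says.** Section 10.2 bases the sample size on percentage inhibition of HSV infection by CVL. In nine naturally cycling women in a pilot study, the mean "at the initial visit was 54 with a standard deviation (sd) of 28". The calculation assumes no true effect ("If we assume that Acidform and HEC have no impact on endogenous anti-HSV activity"), is prepared to "consider 28 (1 sd) as functionally equivalent", and concludes that "a sample size of 18 subjects per arm will provide 80% power to observe statistically significant equivalence of means". No alpha is given. Section 10.3 confirms the allocation: "The randomization will be 1:1 (i.e., 18 in each treatment arm".

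Section 10.1 sets out the analysis of this endpoint in two sentences. In the first, "Differences between groups with respect to endogenous antimicrobial activity of CVL against HSV and" *E. coli* are compared by ANCOVA adjusted for baseline. In the second, the between-group difference in the change in percentage reduction of infection "relative to titers in screening CVL samples will be determined by Wilcoxon nonparametric test (with exact p-values". Neither sentence mentions equivalence, an interval or the value 28, and neither test is put first. Section 10.1 also has a separate Wilcoxon analysis for the 2-hour spiking experiment. That concerns a different measurement and is not at issue here.

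**The concern.** The sample size and the analysis answer different questions. Section 10.2 promises evidence that the two gels are alike to within a stated margin. Section 10.1 can produce evidence that they differ, or a failure to find such evidence. The second of these is not equivalence, because it becomes more likely as the data become noisier.

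This matters because the primary objective is safety, and the reassuring answer is that host defence is not lost. Section 2.1 motivates the trial with products whose harm earlier Phase I work did not predict. Anti-HSV activity is also the only part of the primary objective for which power is stated. Without a rule fixed in advance, nobody can say which results would support the claim the trial was sized to make.

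**Working it through.** **Inputs.** From Section 10.2: sd 28, margin ±28, true difference 0, stated power 80%. From Section 10.3: 18 per arm, so 34 degrees of freedom. Section 10.4 replaces dropouts, so no inflation is applied. Alpha is not stated; I tried one-sided 5% per test.

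**Standard error of the difference.** SE = 28 × √(2/18) = 9.33.

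**Reproducing the 80%.** For two one-sided tests at zero true difference, the normal approximation is 2Φ(margin/SE − 1.645) − 1 = 2Φ(3 − 1.645) − 1 = 82.5%. The exact t-based calculation, integrating over the estimated sd, gives 80.5%. The normal formula also returns the planned size: 2 × (1.645 + 1.282)² × (28/28)² = 17.1, rounded up to 18 per arm. The stated figure is therefore an equivalence calculation that corresponds to a 90% confidence interval within ±28.

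**Where the two procedures part.** If the observed sd is 28:
- the equivalence test passes for an observed difference below 28 − 1.691 × 9.33 = 12.2 points;
- a two-sided 5% t-test is non-significant up to 2.032 × 9.33 = 19.0 points.

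An observed difference between 12.2 and 19.0 points is not significant, yet it does not show equivalence. In simulation, allowing the sd to vary, about 15% of trials with no true difference end in that state. Section 10.1 does not say how to read them.

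**Error rates by true difference (18 per arm, sd 28, no covariate adjustment).**

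| True difference | Two-sided 5% t-test non-significant | Equivalence test passes |
|---|---|---|
| 0 | 95% | 80.5% |
| 14 | 69.2% | 42.8% |
| 28 | 17.0% | 5.0% |

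The last row is the decisive one. At the margin, where equivalence is false, the equivalence test errs at its nominal 5%. Reading non-significance as equivalence would err 17.0% of the time. The middle row is no indictment of the difference test: 14 points lies inside the margin, and the equivalence test itself often passes there.

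**The case against.** The strongest reply is that the planned model is right and only one sentence is missing. ANCOVA yields an adjusted difference with a confidence interval, and that interval can be set against the margin in Section 10.2. This stands, and the fix relies on it. Adjustment may even help: with residual sd 28 × √(1 − ρ²), power for the 90% interval is about 80%, 85% and 92% at assumed baseline correlations of 0, 0.3 and 0.5. The protocol gives no correlation, so these are illustrations only.

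A second reply is that test order, visit and alpha usually belong in a statistical analysis plan. That is fair for detail. It does not remove the mismatch, because the protocol itself names the tests and they do not match its own sizing hypothesis.

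Third, a reader might infer that the team intends to treat a non-significant p-value as proof of equivalence. No sentence says so. The 17% is therefore the price of that reading if it were adopted, not a property of the plan.

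Fourth, a reader might infer that the trial is underpowered, since a 95% interval within ±28 would have only 66% power. The protocol specifies no such interval, and at the 90% level the stated power is met.

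Finally, this is a 36-woman Phase I study whose size is also justified by comparison with similar studies, and clinical safety is analysed separately through adverse events. That limits the consequences but does not supply the missing rule.

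**Conclusion.** The point holds as a mismatch between sizing and analysis. The 80% in Section 10.2 is correct for an equivalence test at one-sided 5% per side (80.5%), but Section 10.1 contains no such test, no alpha for it and no use of the margin. Followed as written, the analysis cannot reach the conclusion the trial was sized for. The size of the issue is 17% against 5% at a true 28-point loss, conditional on non-significance being taken as equivalence, which the protocol does not state. The figures assume normal data, sd 28 in both arms and no gain from baseline adjustment.

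Two further readings go too far. The documents do not support giving anti-HSV activity sole primary status, because Sections 3.1 and 10.1 place antimicrobial activity and the mediators jointly in the primary objective. Nor can one yet say which confidence limit represents harm. Section 10.2 calls the variable inhibition but defines it as plaque formation relative to control, on which a higher value means less protection. The symmetric margin makes the equivalence decision indifferent to this; naming the limit that represents loss is not.

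**What to change.** In Section 10.1, state the following for anti-HSV activity:

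- The decisive visit is Day 14, the end of the dosing period named in the primary objective.
- Equivalence is concluded only if the 90% confidence interval for the ANCOVA baseline-adjusted difference in percentage inhibition (Acidform minus HEC) lies within -28 to +28, which is two one-sided 5% tests.
- Both limits are reported, and the one that represents the largest loss of protection not excluded is identified as such. The margin is wide: 28/54 = 52% of the pilot mean, or 28/46 = 61% if the 54 is really residual plaque formation.
- A non-significant difference is not evidence of equivalence.
- The Wilcoxon test on change from screening is a sensitivity analysis for this endpoint.

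In Section 10.2, state the alpha and correct the definition so that it describes inhibition. Leave *E. coli* and the mediators in the primary objective, and note that the stated power applies to anti-HSV activity only.

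The cost is wording, with no added participants, visits or assays. The one downside for the investigators is a stricter standard for claiming no loss of activity. The change should be made before the analysis, since a rule chosen after seeing the data gives no error control.
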